### Outcome measures

The primary outcome measure is the DASH outcome measure; a validated,
self-reported questionnaire designed to help describe the disability experienced
by people with upper-limb disorders and also to monitor changes in symptoms and
function over time [14-16].The DASH outcome measure is scored in two components: the
disability/symptom section (30 items, scored 1-5) and the optional high
performance Sport/Music or Work section (4 items, scored 1-5). The DASH gives a
score out of 100, in which a higher score indicates greater disability. The DASH
outcome score is validated in both the English and Dutch language.

Secondary outcome measures consist of;

– The Oxford Elbow Score (OES), which reflects both function and
pain following elbow surgery. The OES consists of three domains; pain, function
and social-psychological. Each domain comprises of 4 questions with 5 response
options per question. Each response is scored 0 to 4, with 0 representing
greater severity. Scores for each domain are calculated as the sum of each
individual item score within that domain. These scores are then converted to a
metric score between 0 and 100 (a lower score represents greater severity) [17,18].

– The Mayo Elbow Performance Index (MEPI), which is based on 4
domains (pain, range of motion, stability and elbow function). A total score
between 95 and the maximum 100 points is considered excellent; 80–95 is
good; 60–80 is fair and less than 60 points is poor [19].

– Elbow pain; Pain level will be determined using the Numeric
Rating Scale, an 11–point scale for patient self-reporting of pain

– Active and passive ROM (flexion, extension, pronation,
supination) of both elbow joints will be measured on both sides using a
universal goniometer.

– Crepitance or block to motion will be assessed with elbow and
forearm motion at admission and every follow up visit

– Number of complications (infection, neurovascular compromise,
subsequent or secondary intervention, arthrosis)

– Determining the need for and number of secondary
interventions

– Radiographic appearance of the elbow joint will be evaluated
on the anteroposterior and lateral radiographs at one year. Heterotopic
ossification will be classified as a bone exostosis or as soft tissue
ossification of a ligament, capsule or muscle (“myositis
ossificans”) according the classification scheme of Broberg and Morrey [20]; degenerative changes of the radiocapitellar and ulnohumeral joints

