will be classified as grade zero (no change), grade 1 (slight narrowing of the
joint space with small osteophytes), grade 2 (moderate narrowing of the joint
space, osteophytes and subchondral sclerosis), or grade 3 (severe narrowing of
the joint space, large osteophytes, subchondral sclerosis and cystic
deformation). The final radiographs will also be evaluated for fracture healing
and signs of hardware failure or other complications.

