### Sample size calculation

The primary outcome variable will be the DASH, which has a minimal clinically
important difference of 17 for the elbow [16]. Consequently, a 2-sided unpaired T-test with an alpha-level of 0.05,
a beta-level of 0.1, and an allocation ratio of 1, requires 31 patients in each
group to detect an effect size of 0.85. Anticipating a dropout rate of 25%, a
sample size of 39 patients in each arm is required.

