### Statistical analysis

Normality of continuous data will be tested with the Shapiro-Wilk and
Kolmogorov-Smirnov test as well as by inspecting the frequency distributions
(histograms). Homogeneity of variances will be tested using the Levene’s
test. The analysis will be performed on an intention to treat basis. Patients
with protocol violations will remain in follow-up, and data will be recorded.
Data will be analyzed with and without inclusion of patients with a protocol
violation. Descriptive analysis will be performed to report baseline
characteristics in both treatment groups. For continuous data (e.g. age), means
and standard deviations (parametric data) or medians and percentiles
(nonparametric data) will be calculated. For categorical data (e.g. gender)
frequencies will be calculated.

Patients will be analyzed according to the intention-to-treat protocol. The
primary outcome, DASH at one year will be corrected for age and assessed using
an analysis of covariance (ANCOVA). Trends in DASH scores among the different
time points will be assessed using a repeated measures ANOVA if the data is
normally distributed. The secondary outcomes; MEPI, OES, pain as indicated on a
Numerical Rating Scale (NRS), Range of Motion (ROM) will be analyzed in a
similar manner. The radiological outcome, number of conversions and complication
rate will be determined using either a Fisher Exact or a Chi square test,
depending on the order of magnitude of the results.

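### Only unordered tests are named for the radiological outcome, although it includes arthrosis grades on an ordered 0–3 scale; naming an ordinal test is a cheap improvement

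*Protocol article*

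**What the plan says.** In the protocol article, Outcome measures, radiographs are assessed "on the anteroposterior and lateral radiographs at one year. Heterotopic" ossification is classified by type. Degenerative change of the two joints "will be classified as grade zero (no change), grade 1 (slight narrowing of the" joint space with small osteophytes), and so on up to grade 3 for severe change. Fracture healing and hardware failure are also read from the final films. The same section lists arthrosis a second time, among the complications.

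Statistical analysis covers all of this in one sentence: "The radiological outcome, number of conversions and complication" "rate will be determined using either a Fisher Exact or a Chi square test", the choice between the two depending on how large the results turn out to be. No ordinal or trend test is named for any radiographic item. The article does not say whether the arthrosis grades enter as four levels or are collapsed, and it gives no expected grade distribution, effect or power for them.

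**The concern.** The grades form a severity scale, and the natural question is whether arthrosis is worse in one arm. On a table of 2 arms by 4 grades, Pearson's chi-square and Fisher's exact test give the same p-value however the four grades are relabelled. They ask whether the distributions differ in any way, and spread the signal over 3 degrees of freedom instead of 1.

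The trial is small and was sized for the DASH, so power for a graded secondary outcome is likely to be modest anyway. A moderate but consistent shift in arthrosis could then be missed by a test that does not use the information collected. This is not a detail left for later: the article does name the tests, and they do not match the scale it defines.

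**Working it through.** **Inputs from the protocol article (Sample size calculation).** The DASH comparison is sized with "a 2-sided unpaired T-test with an alpha-level of 0.05". The other inputs given there are power 0.90, equal allocation, a standardised difference of 0.85, 31 per group before losses, and 39 per arm once 25% dropout is allowed for.

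**Reproducing the plan's figure.** The exact t-test solution for an effect size of 0.85, two-sided 0.05 and power 0.90 is 30.08, so 31 per group as stated (power at 31 is 0.909). With 39 enrolled and 25% lost, 39 × 0.75 = 29.25, or about 29 evaluable per arm. The comparison below therefore uses 29, 31 and 39 per arm.

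**Step 1, theory.** Suppose the whole difference lies in the ordered direction. A 1-df test with power P then has noncentrality λ = (1.96 + z_P)². The unordered test has the same λ on 3 df, with power Pr[χ²₃(λ) > 7.815].

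| Power, ordered test (1 df) | λ | Power, unordered test (3 df) | Relative loss |
|---|---|---|---|
| 0.50 | 3.84 | 0.345 | 31% |
| 0.80 | 7.85 | 0.645 | 19% |
| 0.90 | 10.51 | 0.784 | 13% |

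The relative loss is larger where power is low and smaller where it is high.

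**Step 2, simulation.** There were 20,000 trials per scenario, two-sided 0.05, comparing Pearson chi-square on the 2 × 4 table, the tie-corrected Wilcoxon rank-sum test, and a 2 × 2 test of any arthrosis versus none. All grade distributions and odds ratios are assumptions; none comes from the article. The second arm is obtained by dividing each cumulative odds by the odds ratio. For example, with 60/25/10/5% and odds ratio 3, the cumulative odds 1.5, 5.67 and 19 become 0.5, 1.89 and 6.33, so the second arm has 33/32/21/14%.

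Power with 31 per arm:

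| Assumed grades 0/1/2/3 (%) | Odds ratio | Chi-square 2 × 4 | Rank test | Any vs none | Relative loss, chi-square vs rank |
|---|---|---|---|---|---|
| 40/30/20/10 | 2 | 20% | 32% | 24% | 36% |
| 40/30/20/10 | 3 | 48% | 65% | 48% | 27% |
| 40/30/20/10 | 4 | 70% | 85% | 65% | 18% |
| 60/25/10/5 | 2 | 18% | 29% | 29% | 38% |
| 60/25/10/5 | 3 | 45% | 63% | 58% | 29% |
| 60/25/10/5 | 4 | 66% | 82% | 76% | 19% |
| 85/12/2/1 | 2 | 10% | 19% | 19% | 48% |
| 85/12/2/1 | 3 | 26% | 44% | 44% | 40% |
| 85/12/2/1 | 4 | 45% | 66% | 66% | 31% |

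Over all five assumed distributions (also 25/25/25/25 and 70/20/8/2), odds ratios 2 to 4 and 29 to 39 per arm, the relative loss runs from 12% (39 per arm, 40/30/20/10, odds ratio 4: 80% vs 92%) to 48% (31 per arm, 85/12/2/1, odds ratio 2). In absolute terms it is about 8 to 21 percentage points.

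**Step 3, null behaviour.** The rank test rejects in 4.7% to 5.3% of null trials. Chi-square rejects in 2.8% to 5.1%, the low values arising when the upper grades are nearly empty. Part of the largest losses is therefore conservatism from sparse cells as well as lost ordering.

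**Step 4, where the ordered test is worse.** If one arm is 60/25/10/5% and the other 60/5/15/20%, there is no consistent shift. With 31 per arm, chi-square has 62% power and the rank test 11%.

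Fisher's exact test on the 2 × 4 table was not simulated. It shares the indifference to ordering, but its power here is not quantified.

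**The case against.** The strongest reply is that the article never says four grades are tested as four columns. It speaks of the radiological outcome as a whole, alongside conversions and complications. That outcome also contains heterotopic ossification, healing and hardware failure, for which Fisher or chi-square is appropriate. Arthrosis also appears among the complications, so a count of patients with any arthrosis fits the text as well. If most patients are grade 0, that analysis matches the rank test (44% vs 44% at 85/12/2/1%, odds ratio 3).

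This stands as a limit on the claim. It does not remove the point, because no collapse or cut-point is stated. Where arthrosis is more common, collapsing has its own cost (48% vs 65% at 40/30/20/10%, odds ratio 3).

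A reader might infer that the planned test loses about a third of the power. The article does not support that as a fact: it gives no grade distribution or effect. A loss of that order appears mainly where the ordered test itself has low to moderate power; where that test reaches about 90% power, the loss is about 12% to 14%. Every such figure also assumes a proportional-odds shift.

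It is also fair to say that nothing becomes invalid. Neither test exceeds about 5% under the null beyond simulation error, and naming a test does not stop the authors from reporting frequencies by arm, which show direction. Table layout and effect estimates for a secondary item may properly stand in a fuller document.

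**Conclusion.** The point holds in a limited form. The article defines an ordered scale and names only tests that ignore order for the outcome containing it. If the grades are analysed as recorded, power against a consistent shift falls by roughly 12% to 48% in relative terms. That range rests on assumed grade distributions, proportional odds ratios of 2 to 4 and 29 to 39 patients per arm. If the grades are collapsed to any versus none and nearly all patients are grade 0, the loss is close to zero.

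The text does not establish that a four-column table is planned, nor any single figure for the loss. One secondary outcome is affected; the primary DASH comparison and the sample size are not. This is a cheap improvement.

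**What to change.** Add one sentence to Statistical analysis: the 0–3 arthrosis grades for each joint will be compared with a Wilcoxon rank-sum test or a proportional-odds model, reporting the common odds ratio with its 95% confidence interval. Keep Fisher or chi-square for the binary and nominal items: heterotopic ossification, healing, hardware failure, conversions, and complications. If a collapsed analysis is intended instead, state the cut-point before the data are seen.

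No new data, visits or patients are needed. There are two small downsides. An ordered test has less power if the arms differ without a consistent shift, and the common odds ratio assumes proportional odds. Tabulating the four grades by arm would let readers see either problem.

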### Ethical considerations

Considering current evidence, no clear preference exists for either one of the
treatment allocations in this study. Both treatment modalities are regularly
applied for these fractures in each of the participating institutions. All
surgeons participating in this study are familiar with nonoperative and
operative management of patients with radial head fractures. Except for the
assignment of treatment, management will not differ from patients with similar
conditions that are not enrolled in the study. Patients will be exposed to
radiation from radiographs. However, this exposure is part of routine clinical
care and represents no increased risk. No additional radiographs will be made as
part of this study. The risks and discomfort of participating in this study do
not exceed those of expected of standard treatment for this condition. Patients
may be inconvenienced by the questionnaires, but we consider this a minor
inconvenience, as they will take approximately 10 minutes to complete and can be
filled in online.

There is no incentive for patients to participate in this trial. The motivation
for the study is a potential benefit to all patients with radial head fractures,
as we increase our knowledge on optimal treatment of these fractures.

### Monitoring and quality assurance

This study has been approved by the Institutional Review Board of the principal
investigators hospital under the number: NL38903.008.11. Approval of local
Medical Ethical Committees will be obtained in all participating hospitals
separately. At the time of press, local approval was already obtained for 5 out
of 9 participating hospitals. All signed informed consent forms will be filed in
locked cabinets in research offices. Any personal information collected during
this study will be placed in a research folder, and not added to the
patient’s medical record unless expressly requested by the patient.
Functional results (range of motion, complications) and questionnaires will be
collected digitally and stored on a password-protected, secured server to which
only study staff will have access. Apart from date of birth of included
patients, no personal data will be stored digitally.

A member of the study staff will be responsible for monitoring outcomes. No
independent monitoring will occur. All investigators and study staff will be
responsible for reporting adverse effects to the coordinating investigator. Our
coordinating investigator will report adverse events to the ethical committee in
accordance with the ethical committee adverse event reporting procedures. The
coordinating investigator and the principal investigator are responsible for
adherence to all ethical committee rules and guidelines and for the accuracy and
completeness of all forms, entries, and informed consent.

## Discussion

To date there have been no prospective randomized trials comparing nonoperative
treatment and ORIF for stable, displaced, partial articular fractures of the radial
head. The RAMBO trial will compare management of these fractures of the radial head
by nonoperative treatment and ORIF. ORIF may lead to a better ROM, but may also
carry a higher risk of complications. Patient enrollment has started in November
2012 and we expect to enroll 4 patients per month. Considering the one-year
follow-up, publication of data will be expected in 2015.

## Abbreviations

AO: Arbeitsgemeinschaft für Osteosynthesefragen (German for “Association
for the Study of Internal Fixation”); AP: Anteroposterior; CT: Computed
tomography; DASH: Disabilities of the arm, shoulder and hand score; ISS: Injury
severity score; MEPI: Mayo elbow performance index; NRS: Numeric rating scale; NTR:
Netherlands trial registry (in Dutch: Nederlands Trial Register); OES: Oxford elbow
score; RAMBO: Radial head – amsterdam – amphia – boston - others;
ORIF: Open reduction and internal fixation; ROM: Range of motion; SPSS: Statistical
package for the social sciences.
